### Interventions

2.4

The interventions in this study will be conducted for 12 weeks. Game-based circuit exercise group will receive a set of exercise tasks consisting of a) resistance exercises including sit to stand, partial squat, step up down, hip raise and heel raise, b) balance exercises including figure of 8 walking, tandem walking, backward walking, walking with instruction and walking with sudden change direction and c) aerobic exercises including punching jab, hook, cross straight and combination punching maneuver with squat and kicking, which aim to improve muscle strength, postural stability and aerobic endurance.

This game-based circuit exercise will use a specially designed exercise board namely Checkercise board (Fig. 2). The design of the Checkercise is similar to the “snake and ladder” game board. To use the Checkercise board, the participants will first be required to place their counter on the space that indicates “start.” Then, they have to take a turn to roll a dice. Next, they have to move their counter forward by several spaces based on the number as shown on the rolled dice. Exercises to be performed by the participants will depend on where their counter land on the board each time the dice is rolled, as each space shows a different exercise task. There is also a possibility of being penalized during the exercise if their counter lands on “penalty spaces,” such as spaces which indicate “slide back a few spaces,” and “move to a certain board number.” The game-based circuit exercises are considered complete when participants arrive at a space that indicates “finish.” The main researcher will supervise the participants in performing the Checkercise board exercise in the group of 4 participants per session. Exercise duration in each space is 2 minutes interspersed by 2 minutes rest with a total of ten exercises to be performed in average for a duration of 40 minutes. Participants will perform the given exercises at a comfortable pace for 2 times per week, under close monitoring by the main researcher. Exercise adherence and the level of exercise intensity (e.g., low, moderate, vigorous) will be monitored using sessions attendance checklist and Borg Scale Rate of Perceived Exertion, respectively. Table 1 shows the frequency, intensity, time and type (FITT) principle of the Checkercise board exercises to be provided to participants in game-based circuit exercise group.

**Figure 2 F2:**
[figure not shown]
Part of the Checkercise board exercise.

**Table 1 T1:** Description of game-based circuit exercise in the checkercise board.

Formula	Resistance exercise	Balance exercise	Aerobic exercise
	**Repeated sit to stand**	**Walking on balance beam**	**Alternate jab**
Frequency	2 sessions/wk	2 sessions/wk	2 sessions/wk
Intensity	Speed at 50 beats per min	Speed at 30 beats per min	Speed at 100 beats per min
Time	1 min	1 min	1 min
Technique	Alternate seated to standing (without load)	Walking on balance beam (follow rhythm)	Repeated jab punching (follow rhythm)
Progression	Alternate seated to standing (Lifting up 2 kg of dumbbell)	Tandem walking (follow rhythm)	Repeated double jab punching with defense (follow rhythm)
	**Repeated partial squat**	**Figure of 8 walking**	**Alternate hook**
Frequency	2 sessions/wk	2 sessions/wk	2 sessions/wk
Intensity	Speed at 30 beats per min	Speed at 45 beats per min	Speed at 100 beats per min
Time	1 min	1 min	1 min
Technique	Standing, partial squats with arm support as needed (without load)	Figure of 8 walking (follow rhythm)	Repeated hook punching (follow rhythm)
Progression	Standing, partial squats with arm support as needed (Lifting up 2 kg of dumbell/speed at 50 beats per min)	Figure of 8 walking while holding cup of water	Repeated alternate hook with kicking (follow rhythm)
	**Repeated step up & down**	**Walking with instruction**	**Double jab & hook**
Frequency	2 sessions/wk	2 sessions/wk	2 sessions/wk
Intensity	Speed at 70 beats per min	-	Speed at 100 beats per min
Time	1 min	1 min	1 minute
Technique	Standing, alternate steps-ups on the 8-inches step (without load)	Walking & stop (closed eyes in static standing)	Repeated double jab punching with hook (follow rhythm)
Progression	Standing, alternate steps-ups on the 8 inches step board (Lifting up 2 kg of dumbbell/speed at 75 beats per min)	Walking while sudden change instruction	Repeated double jab punching with hook & squat (follow rhythm)
	**Standing; repeated hip raise**	**Walk & touch cones**	**Double jab**
Frequency	2 sessions/wk	2 sessions/wk	2 sessions/wk
Intensity	Speed at 45 beats per min	Speed at 20 beats per min	Speed at 100 beats per min
Time	1 min	1 min	1 min
Technique	Standing, alternate steps-ups on the 8-inches step board (without load)	Walk & touch cones cuboid shape (follow rhythm)	Repeated double jab punching with defense & kick (follow rhythm)
Progression	Standing, alternate steps-ups on the 8-inches step board (Lifting up 2 kg of dumbbell/speed at 50 beats per min)	Walk & touch cones hexagon shape (follow rhythm)	Repeated double jab punching with squat (follow rhythm)
	**Standing; repeated heel raise**	**Backward walking**	**Cross straight**
Frequency	2 sessions/wk	2 sessions/wk	2 sessions/wk
Intensity	Speed at 70 beats per min	Speed at 45 beats per min	Speed at 100 beats per min
Time	1 min	1 min	1 min
Technique	Standing, alternate raises heel (without load)	Backward walking (follow rhythm)	Repeated cross straight punching (follow rhythm)
Progression	Standing, alternate raises heel (Lifting up 2 kg of dumbbell/speed at 75 beats per min)	Backward walking (follow rhythm for 2 min)	Repeated 4 times cross straight punching with squat (follow rhythm)

Meanwhile, participants in the control group will be supervised by 2 physiotherapists to perform the conventional circuit exercises in a group of 5 participants per session. The participants will take turn to perform exercise tasks which are organized in a total of 6 stations, consisted of;

1.cycling,2.repeated sit to stand,3.repeated arm curl,4.repeated hip & heel raise,5.stepping up and down and6.obstacle walking.

The exercise duration in each station is 5 minutes interspersed by a 2-minute rest. Similar to the experimental group, all participants in this control group will receive an exercise session of 40 minutes, twice per week for 12 weeks.

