### Sample size

2.7

The required sample size for this study was estimated using GPower software version 3.0.10. This study will use mixed model analysis of variance (ANOVA) to analyze time, group and interaction effects of the interventions. Therefore, F-test (ANOVA repeated measure, within-between interactions) was chosen and inputted into the system. The study power and alpha value was set at 80% and 0.05, respectively. Based on these inputs, a minimum sample of 82 subjects is required, that is, 41 participants in each trial group.

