### Data analysis

2.8

All data will be entered into IBM Statistical Packages for Social Sciences (SPSS) version 25.0. Intention-to-treat (ITT) analysis approach will be used; all the recruited participants will be included in the outcome analysis. Using ITT approach, missing data will be replaced with “last observation carried forward.” Socio-demography and health profile of the participants will be analyzed descriptively and reported as frequencies (percentages) and mean (standard deviation) or median (inter-quartile range). The effects of the interventions will be analyzed using mixed model ANOVA and reported as main time, group and time-group interaction effects for each outcome variable. Level of significance is set as *P* < .05 for all results.

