## Discussions

3

Circuit exercise training has been shown to benefit stroke survivors in improving their functional performance through exercising in group under therapists’ supervision. However, evidence on including enriched and fun environment into the existing format of circuit exercise to make it more challenging and interesting particularly for stroke survivors is still limited, which warrants more studies on this topic area. The nature of each exercise task in the designed Checkercise board will offer such targeted environment by adding multisensory stimulation and cueing, cognitive stimulation and limb integration training to further increase neuroplasticity potentials.

Further, the presence of fun and enjoyment through competition could be a factor affecting stroke survivors’ motivation and adherence level during exercise training. We believe that the game-based component of our circuit exercise training will induce these positive influences. Within the fun environment, participants will compete and work hard to achieve their best level exercise performance, hence would induce better functional recovery through enhanced neuroplasticity.

This proposed study is expected to fill the gaps in knowledge and strengthen evidence on the benefit of game-based circuit exercise for stroke survivors. This study will also compare game-based circuit exercise with the existing circuit exercise for stroke survivors and provide information whether game-based circuit exercise is a better approach for this group of population in preventing long-term functional problems. It is our hope that findings from this study can be used to enable rehabilitation professionals to design more interesting, creative and effective exercise training in stroke rehabilitation and serve as a reference for future studies regarding game-based circuit exercise.

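### Both arms train in small groups, but the planned ANOVA and the sample size treat all 82 participants as independent, so the type I error may exceed 5% if outcomes correlate within groups.

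*Protocol article*

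**What the plan says.** All places are in the protocol article.

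- **Section 2.4, game-based arm:** "The main researcher will supervise the participants in performing the Checkercise board exercise in the group of 4 participants per session".
- **Section 2.4, control arm (text after Table 1):** two physiotherapists supervise participants, who "perform the conventional circuit exercises in a group of 5 participants per session".
- **Section 2.4, both arms:** two sessions per week for 12 weeks, which is 24 sessions.
- **Section 2.3:** allocation is by individual participant within age and disability strata.
- **Section 2.7:** the sample size rests on an individual-level test: "Therefore, F-test (ANOVA repeated measure, within-between interactions) was chosen and inputted into the system". With 80% power and alpha 0.05, the article concludes that "a minimum sample of 82 subjects is required, that is, 41 participants in each trial group".
- **Section 2.8:** "The effects of the interventions will be analyzed using mixed model ANOVA", reported as time, group and time-by-group effects for each outcome, each tested at the 0.05 level.
- **Section 3, on the game-based format:** "Within the fun environment, participants will compete and work hard to achieve their best level exercise performance".

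No section mentions exercise group as a source of correlation, an ICC or a design effect. The article does not say whether the same people stay together through the 24 sessions. Attendance is tracked on a checklist, and no group identifier is mentioned.

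**The concern.** People who train together share sessions, pace and atmosphere. In the game-based arm they also take turns on one board, and the authors expect competition to raise effort. That is a plausible route to correlated outcomes within an exercise group. Motivation and effort-dependent tests, such as the chair rise and the 6-minute walk, look the most exposed.

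Individual randomisation does not remove correlation that arises after allocation from shared delivery. The repeated-measures part of the planned ANOVA does not remove it either: it handles correlation between visits of one person, not between people in the same group. If the correlation is positive, each arm mean is less precise than the model assumes. P-values are then too small, confidence intervals too narrow, and real power lower than planned.

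**Working it through.** **Inputs from the article.** 41 participants per arm, alpha 0.05 and power 80% (section 2.7). Group sizes 4 and 5 (section 2.4), so about 41/4 ≈ 10 and 41/5 ≈ 8 groups. Four measurement times: baseline, end of the intervention, and 12 and 24 weeks later (section 2.6).

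**Assumed, because the article does not give them.** Stable groups; ICC of 0, 0.01, 0.05, 0.10 and 0.20; within-person correlation of 0.5 and 0.7.

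**The plan's own figure.** The 82 cannot be reproduced from the stated inputs, because the effect size, within-person correlation and number of measurements entered are not given. For the named interaction test, 82 results from an effect size f of about 0.13 with four measurements and correlation 0.5, or from f = 0.20 with three measurements and correlation 0. Neither calculation has a cluster term.

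**Step 1: design effect.** DE = 1 + (m − 1) × ICC, that is 1 + 3 × ICC in the game-based arm and 1 + 4 × ICC in the control arm. With the mean of the two, the true standard error is √(mean DE) times the one assumed. For example, at ICC 0.05: DE = 1.15 and 1.20, mean 1.175, √1.175 = 1.08.

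**Step 2: single-comparison approximation.**
- Type I error of the unadjusted test = 2 × (1 − Φ(1.96/√DE)).
- Power of a valid test = Φ(2.80/√DE − 1.96), where 2.80 = 1.96 + 0.84.
- Effective N = 41/DE₄ + 41/DE₅.
- N needed = 41 × DE₄ + 41 × DE₅, each rounded up.

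| ICC | DE (4 / 5) | SE ratio | Type I error | Power | Effective N | N needed |
|---|---|---|---|---|---|---|
| 0 | 1 / 1 | 1.00 | 5.0% | 80% | 82 | 82 |
| 0.01 | 1.03 / 1.04 | 1.02 | 5.4% | 79% | 79 | 86 |
| 0.05 | 1.15 / 1.20 | 1.08 | 7.1% | 73% | 70 | 98 |
| 0.10 | 1.30 / 1.40 | 1.16 | 9.2% | 67% | 61 | 112 |
| 0.20 | 1.60 / 1.80 | 1.30 | 13.3% | 57% | 48 | 140 |

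The power column is an upper limit, because it uses 1.96 although there are only about 18 groups. With a t critical value on 18 − 2 = 16 degrees of freedom, the lowest reasonable number, power is about 68% at ICC 0.05 and 62% at 0.10.

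**Step 3: the test that is actually planned.** The 2 × 4 mixed ANOVA was simulated 20,000 times per setting under no treatment effect, with 10 and 8 fixed groups and a shared group effect on the three post-baseline visits. Rejection rates of the time-by-group test at nominal 5%:

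| ICC | Within-person correlation 0.5 | Within-person correlation 0.7 |
|---|---|---|
| 0 | 4.9% | 4.8% |
| 0.01 | 5.5% | 5.3% |
| 0.05 | 6.5% | 8.1% |
| 0.10 | 9.4% | 12.0% |
| 0.20 | 13.9% | 18.6% |

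The main effect of arm gave 6.8 to 6.9% at ICC 0.05 and 8.5 to 8.9% at ICC 0.10.

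**Step 4: what kind of model term helps.** A random intercept for exercise group that is constant over time adds the same amount to every visit of a person. It therefore cancels from every within-person contrast, and so from the time-by-group test. An effect that starts after baseline does not cancel. To correct the interaction test, the model term must act on the post-baseline visits.

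**The case against.** **The excess is not established.** A reader might infer that the 5% level will be exceeded. The article does not support that. It gives no ICC, and 4 and 5 participants per session may describe session capacity and not fixed groups. Rotating membership would weaken any correlation. This stands, and the point is therefore conditional.

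**Competition concerns one arm.** A reader might also infer that competition links outcomes in both arms. Sections 2.4 and 3 describe it for the game-based format only, and tentatively. In that arm each person's exercises follow from their own dice rolls, and competition could produce winners and losers within a group, so even the sign of the correlation is not certain. This stands. Shared sessions remain a plausible source of correlation in both arms, but a weaker one in the control arm.

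**Supervisors differ little within an arm.** The main researcher supervises the game-based sessions and two physiotherapists the control sessions. As described, differences between therapists add little variation between groups of one arm. This is a reason not to assume a high ICC, but it does not remove the effect of training with the same people.

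**The article may leave this to a fuller plan.** Random-effect structure often sits in the SAP, which is not shown. But the article does not leave the analysis open: it names the model, its effects and a matching individual-level sample-size test. Group membership also has to be recorded during delivery, and a later plan may be unable to recover it.

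**The simple formula is not the planned test.** True. The type I error in the verdict is therefore taken from the simulated interaction test, and the formula's power is given only as an upper limit.

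**Conclusion.** The point holds in conditional form. Both arms are delivered in groups, and the stated analysis and sample size ignore this. With reasonably stable groups and a positive ICC, the type I error of the time-by-group test is about 5.5% at ICC 0.01 (negligible), 6.5 to 8% at 0.05 and 9 to 12% at 0.10, depending on within-person correlation. A nominal 80% power falls to at most about 73% at ICC 0.05 and 67% at 0.10, and somewhat lower with small-sample degrees of freedom. The ICC range, fixed membership and within-person correlations are assumptions, not figures from the article. The change should be made: the protection is cheap, and little is lost if the ICC proves to be near zero.

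**What to change.** 1. **Section 2.4:** state whether exercise groups are fixed for the 12 weeks, and record each participant's exercise-group identifier on the attendance checklist.
2. **Section 2.8:** replace the mixed model ANOVA by a linear mixed model with time, arm and time-by-arm effects, the repeated measures within person, and exercise group nested in arm as a random effect on the post-baseline visits (a group-by-time effect). A constant group intercept alone would leave the time-by-group test uncorrected. Use Satterthwaite or Kenward-Roger degrees of freedom. Separate group variances by arm should be optional, because about 10 and 8 groups estimate them poorly.
3. **Section 2.7:** restate the power of 82 participants over an assumed ICC range, with design effects 1 + 3 × ICC and 1 + 4 × ICC.

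**Cost:** one more recorded field, a slightly more complex model, somewhat wider confidence intervals and a less favourable stated power. The analysis change itself needs no extra participants. Holding 80% power would need about 98 at ICC 0.05 or 112 at ICC 0.10 before allowing for small-sample degrees of freedom, so the sponsor should either accept the lower power openly or revisit the sample size.

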### Outcomes

2.5

Functional performance among the participants will be assessed in term of lower limb strength, dynamic balance and aerobic endurance.

A 30-second chair rise test will be used to assess lower limb strength. The normal cutoff chair rise repetition is between 14 to 17 and 13 to 15 for healthy male and female aged 55 to 75 years old, respectively.^[29]^ 30-second chair rise test was shown to have high test-retest reliability (ICC = 0.89) and moderate correlation with the leg press test in stroke survivors (*r* = 0.77).^[29]^ Participants will be instructed to repetitively stand up from a 42 cm high and 47.5 cm deep chair while their arms crossed as quickly as possible within 30 seconds. The number of complete sit to stand tasks performed in 30 seconds will be recorded.The Dynamic Gait Index (DGI) will be used to evaluate dynamic balance in walking. The normal cutoff mean score is between 23.2 ± 0.9 to 23.9 ± 0.4 for healthy individual aged 50 to 79 years old.^[30]^ The participants will be instructed to perform all 8 walking tasks, which consisted of1.walking on level surface,2.walking while changing speed,3.walking while turning head horizontally,4.walking while turning head vertically,5.walking with a pivot turn,6.stepping over obstacles,7.stepping around obstacles, and8.stair climbing. Each task is scored using a 4-point ordinal scale ranging from 0 (severe impairment) to 3 (normal).The DGI was shown to have high test-retest reliability (ICC = 0.94–0.96)^[31,32]^ and moderate to excellent correlation with the Timed-Up and Go test, 10-meter walk test and Activities-specific Balance Confidence scale in stroke survivors (*r* = 0.68–0.83).^[31]^ The total score ranges from 0 to 24 and a higher total DGI score signifies a higher level of independence in functional mobility among stroke survivors.A 6-minute walk test (6 mWT) will be used to measure aerobic endurance. The normative data for mean walked distance is between 357 to 697 meters and 421 to 795 meters for healthy male, and 321 to 621 meters and 392 to 765 meters for female aged 50 to 79 years old.^[33]^ The 6 mWT was shown to have high test-retest reliability (ICC = 0.99)^[34]^ and moderate to excellent correlation with the 2-minute walk test, 12-minute walk test and maximum oxygen uptake in stroke survivors (*r* = 0.66–0.99).^[34,35]^ Participants will be instructed to walk at a comfortable pace along a marked walking course of ten meters in length. The total distance walked in 6 minutes will be recorded in meters.

Motivation level with regard to experimental tasks will be assessed using a Multidimensional Intrinsic Motivation Inventory (IMI). The inventory consists of 4 subscales with a total of 22 questions that can be calculated separately;

1.interest and enjoyment (8 questions);2.perceived competence (5 questions), perceived choice (5 item) and pressure and tension (5 item).

The IMI has adequate reliability value, indicated by Cronbach's α coefficient (ICC = 0.85).^[36]^ The score ranges from 1 to 7 (1 indicates “not at all true”; 4 indicates “somewhat true”; 7 indicates “very true”) and a higher total score signifies a higher level of motivation level (high 7.00–4.67; average 4.66–2.34; low 2.33–1.00).

Self-efficacy: The stroke self-efficacy questionnaire (SSEQ), a 13-item self-administered questionnaire which designed specifically for stroke survivors will be used to assess the level of self-efficacy among the study participants. SSEQ consists of 2 self-efficacy domains: activity (items 1–8) and self-management (items 9–13).^[37]^ Participants need to rate their confidence level on a 3-point scale, from 0 which indicates “not at all confident” to 3 which represents “very confident.” The total score of SSEQ will be calculated by summation of each item score. Higher score of SSEQ indicates higher self-efficacy level. SSEQ has good reliability, with Cronbach α coefficient value 0.90 and person separation index (PSI) >0.80 for both activity and self-management domains.^[37]^ The SSEQ was shown to have high test-retest reliability in stroke survivors (ICC = 0.86)^[38]^ and excellent correlation with the Fall Efficacy Scale (*r* = 0.803).^[37]^

Quality of life: Short Form-36 (SF-36) will be used to measure quality of life of the participants. SF-36 contains 8 domains (36 questions) and can be calculated separately which is divided into;

1.physical health component represented by physical functioning (10 questions), role limitation due to physical health (4 questions) and pain (2 questions),2.mental health component represented by social functioning (2 questions), role limitation due to mental problem (3 questions) and emotional wellbeing (5 questions); and3.physical and mental health component represented by general health (5 questions) and energy/fatigue 4 questions).

The SF-36 was shown to have moderate to high test-retest reliability in stroke survivors (0.57<ICC<0.8)^[39]^ and adequate to good correlation with the EuroQol (*r* = 0.66),^[39]^ EQ-5D Index (*r* = 0.68)^[40]^ and Health Related Quality of Life in Stroke Patient (0.47<r<0.79).^[41]^ The total score ranges from 0 to 100, with higher scores indicating a better quality of life.

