### Study participants

2.2

Eligible participants will be recruited by the main researcher using the following inclusion criteria:

1.Clinically diagnosed either hemorrhagic or ischemic stroke by a medical or neurology physician.2.Age 40 to 80 years old (to minimise risk of frailty which is prevalent in those above 80).^[28]^3.Able to perform basic activities of daily living such as walking and turning, stepping up and down steps with or without a walking aid and hold a glass full of water with the non-affected hand.

Exclusion criteria are:

1.Score below 20 on Montreal Cognitive Assessment (MoCA) which indicates the presence of cognitive impairment2.Presence of other neurology or medical conditions which limit physical function such as Parkinson's disease, severe musculoskeletal disorders, unstable angina or uncontrolled hypertension.3.Score 4 or more on a Modified Rankin Scale (4: moderate severe disability; 5: severe disability; 6: death)4.Attended by a home physiotherapist after discharged from in-patient setting or attending a traditional therapy.5.Has visual field defects

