### Participants’ allocation

2.3

Selected stroke survivors will be randomized into either game-based circuit exercise (experimental group) or conventional circuit exercise (control group) using a stratified randomization method, with the use of sealed opaque envelopes by an independent researcher. Stratification variables are age, consisting of younger (40–59 years) and older adults (60–80 years), and disability level, namely 1 (no significant disability), 2 (slight disability) and 3 (moderate disability). Using the sealed envelope system, recruited participants will be stratified according to the sequence of age and disability level. Participants are then alternately allocated into each trial group according to their age and disability level categories. In this way, both the game-based circuit exercise and conventional circuit exercise trial group will consist of participants with comparable age and disability levels.

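### A ceiling on the Dynamic Gait Index is foreseeable: it could understate a balance benefit and hide later loss, and the planned analysis makes no provision for it

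*Protocol article*

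**What the plan says.** Section 2.5 (Outcomes) uses the DGI to assess dynamic balance. No other outcome measures postural stability. The total is the sum of eight items: "Each task is scored using a 4-point ordinal scale ranging from 0 (severe impairment) to 3 (normal"). On the total it says: "The total score ranges from 0 to 24 and a higher total DGI score signifies a higher level of independence in functional mobility". For reference values it says: "The normal cutoff mean score is between 23.2 ± 0.9 to 23.9 ± 0.4 for healthy individual aged 50 to 79 years old".

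Section 2.2 (Study participants) requires an entrant to be "Able to perform basic activities of daily living such as walking and turning, stepping up and down steps with or without a walking aid". It excludes a "Score 4 or more on a Modified Rankin Scale" and sets no DGI or balance-deficit criterion. Section 2.3 (Participants' allocation) stratifies by "disability level, namely 1 (no significant disability), 2 (slight disability) and 3 (moderate disability").

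Section 2.8 (Data analysis) treats all outcomes alike: "The effects of the interventions will be analyzed using mixed model ANOVA and reported as main time, group and time-group interaction effects for each outcome". The introduction makes persistence of any gain at 12 and 24 weeks after the trial a stated aim.

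**The concern.** A participant at the healthy norm has less than one DGI point left to gain. The entry rules admit people with little disability, and both arms exercise for 12 weeks, so some participants may reach 24 by the end of treatment. Beyond that point the scale records no further improvement.

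Two consequences follow if the share at 24 is large:

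- The arm that improves more loses more of its gain to the cap. The between-arm difference in scored DGI then falls below the difference in underlying balance, and power falls with it.
- At follow-up, a participant whose ability declines but stays above the cap still scores 24. The score then shows no loss, which favours a claim of durable benefit.

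Because the DGI is the sole balance outcome, no other measure in the plan would expose either misreading.

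**Working it through.** **Inputs from the protocol.** DGI maximum 24; healthy means 23.2 (SD 0.9) and 23.9 (SD 0.4); 41 participants per arm; two-sided alpha 0.05. The protocol gives no expected DGI mean, SD, share at maximum or target difference for stroke participants, so it has no DGI figure to reproduce.

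**Headroom at the healthy norm.** 24 − 23.2 = 0.8 points and 24 − 23.9 = 0.1 points. If the norms are read as rounded normal distributions, the share of healthy people scoring 24 is 1 − Φ((23.5 − 23.2)/0.9) = 37% and 1 − Φ((23.5 − 23.9)/0.4) = 84%. This describes healthy people, not the trial population.

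**Assumptions for the trial population (none are in the protocol).** Underlying balance is normal with SD 3. The baseline-to-week-12 correlation is 0.7. The gain is 1.5 points in the control arm and 3.0 in the game arm, so the true difference is 1.5. Scores are rounded and limited to 0–24.

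**Expected scored difference.** For an underlying mean μ, the expected score is the sum over j = 1 to 24 of [1 − Φ((j − 0.5 − μ)/3)]. Take μ = baseline + 1.5 for control and baseline + 3 for the game arm:

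- Baseline 14: 16.99 − 15.50 = 1.49, a loss of under 1%.
- Baseline 17: 19.87 − 18.46 = 1.41, loss (1.5 − 1.41)/1.5 = 6%.
- Baseline 20: 22.24 − 21.16 = 1.08, loss 0.42/1.5 = 28%.
- Baseline 22: 23.24 − 22.54 = 0.70, loss 0.80/1.5 = 53%.

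Simulated trials with 41 per arm gave 1.47, 1.40, 1.14 and 0.70, which are losses of 2%, 7%, 24% and 53%. The gaps from the direct calculation are simulation error.

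**Share at 24 and power at week 12.** The share of the game arm at 24 is 1 − Φ((23.5 − baseline − 3)/3).

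| Baseline mean | Game arm at 24 | Power, baseline-to-week-12 interaction (change score) | Power, linear model adjusted for baseline | Power, Tobit adjusted for baseline |
|---|---|---|---|---|
| 14 | about 2% | 0.82 | about 0.87 | 0.87 |
| 17 | 12% | 0.75 | 0.86 | 0.88 |
| 20 | 43% | 0.64 | 0.81 | 0.85 |
| 22 | 69% | 0.36 | 0.64 | 0.71 |

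Most of the recoverable power comes from baseline adjustment: at a mean of 22, 0.36 rises to 0.64, and Tobit adds a further 0.07. With no true difference, the change-score test rejected in about 5% of trials.

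**Other assumptions.** With a true benefit of 2 points, SD 2 to 4 and control gain 1 or 2, the share of the benefit that survives the cap is 96–100% at a baseline mean of 14, 89–100% at 16, 77–97% at 18, 60–83% at 20 and 32–50% at 22. With an assumed equal mix of strata (means 22, 20 and 16, SD 2.5, true difference 1.5), the recovered difference is 1.10, a loss of 0.40/1.5 = 27%, with 39% of the game arm at 24.

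**Limit of the check.** The power figures compare baseline with week 12 only. The planned ANOVA would cover four assessments, and that test was not simulated.

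**The case against.** The strongest reply is that nothing in the protocol shows participants starting near the cap. Being able to walk, turn and climb steps, possibly with an aid, is not the same as being rated normal on those tasks. Speed changes, head turns and obstacles make up five of the eight items and are not in the entry criterion. Moderate disability is also enrolled, no stratum has a quota, and a disability grade does not give a DGI score. All of this stands. At baseline means of 14 to 16 the loss is 0–11% across the assumptions tried.

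A reader might also infer that the cap is itself the healthy norm, that a real benefit will be understated, or that ANOVA is the wrong method. The documents support none of these. The norm is 23.2 to 23.9. Understatement is conditional on an unknown baseline. ANOVA estimates the mean difference in scored DGI without inflating false positives. Any shortfall comes from the instrument and the eligibility rules.

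The alternative model also has limits. Tobit recovers the true difference in simulation partly because the data were generated from the normal latent scale it assumes. In one check with 500 trials per setting its likelihood-ratio test gave 6.0–6.4% false positives. No model can separate participants who all score 24. This is why it belongs beside the main analysis and should not replace it.

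Finally, ceiling reporting could sit in an unseen analysis plan. That limits the criticism but does not remove it, because the article itself fixes one analysis for every outcome.

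**Conclusion.** The point holds as a foreseeable risk, not as a demonstrated bias. The cap, the near-cap norms, the absence of a DGI entry limit and the uniform ANOVA are all stated in the protocol. If a substantial share of participants reaches 24, the scored difference will understate the difference in underlying balance, and a stable score at follow-up will not show that ability was kept.

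Under SD 3, correlation 0.7 and a true difference of 1.5 points, the effect is negligible at a baseline mean of 14, small at 17, about a quarter of the benefit at 20 and about half at 22. Which of these applies cannot be told from the documents. The DGI is one of six measures and the article names no primary outcome, so the consequence is confined to conclusions about balance.

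**What to change.** In section 2.8, for the DGI:

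1. Compare arms with a model adjusted for baseline DGI.
2. Prespecify a sensitivity analysis that treats 24 as right-censored (Tobit) or uses an ordinal model of the total.
3. Report the share of participants at 24 by arm and visit.
4. State that, where a substantial share is at 24, a null difference will not be read as no effect, nor an unchanged follow-up score as no loss.

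No new test, visit or participant is needed. The cost is some wording and one extra model. Tobit brings a latent-normality assumption. The ordinal model reports an odds ratio and not a difference in points. If few participants reach 24, the additions cost essentially no power.
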